## Discussion

The WHO estimates that chronic disease is the cause of the majority of premature deaths in the world and that most of these could be prevented by giving people better access to appropriate health care and treatment and by reducing modifiable risk factors such as diet, exercise, and smoking [2]. Worldwide, the proportion of women of childbearing age living with one or more chronic diseases is growing [3, 5], and pregnancies affected by chronic disease are associated with a higher risk of complications [6, 10] and poor psychological health [8, 47].

The perinatal period is theoretically a favorable time in a woman’s life to implement effective preventive and health-promoting interventions in women [48]. Interventions delivered in the perinatal period can therefore hypothetically reduce the potentially negative health impact in pregnancy caused by chronic disease and possibly also empower and strengthen the women’s long-term self-care ability with their chronic disease.

The ChroPreg trial is highly relevant, and to the best of our knowledge, it is the largest RCT designed to investigate the effect of a midwife-coordinated, individualized, and specialized maternity care add-on intervention for pregnant women with chronic diseases on LOS, patient-reported outcomes, and pregnancy and delivery outcomes.

Systematic reviews of RCTs have found previous complex maternity care interventions to be cost-effective compared with standard care [24, 25]. However, in these reviews, the authors have called for trials that evaluate psychological well-being and patient satisfaction with maternity care with validated psychometric instruments [19, 49]. Therefore, in this RCT, we will use validated patient-reported questionnaires to estimate psychological well-being during pregnancy and postpartum [35, 36, 40], health-related quality of life [43], and patient satisfaction with maternity care [45].

In this trial, we will also combine face-to-face consultations with add-on telephone support and e-mail correspondence delivered by the SM who follow the participants throughout pregnancy and postpartum. Telephone support during pregnancy and after birth has been suggested to be of benefit to women at risk of depression, reducing signs of depression and facilitating breastfeeding initiation and continuation [26]. However, these interventions have not yet been tested among pregnant women with chronic diseases, and therefore the results of this trial may provide information on how to design future woman-centered and cost-effective interventions for women with chronic disease. This trial will also provide information to clinicians about the feasibility of prolonging midwifery care with consultations and more thorough follow-up after discharge from the hospital, because this care currently is delivered primarily by health visitors in Denmark.

Because this is a low-risk intervention adding to standard care and not involving any known side effects, we anticipate that most eligible women with chronic disease will be interested in participating in the trial, and we do not expect a high number of dropouts. Measures to monitor and enhance adherence to the intervention will be taken. The two self-reported questionnaires, one at 33–37 weeks of pregnancy and one at 2 months postpartum, will be followed by reminders if not completed within the time frame, and text message reminders will be sent in advance; adherence to all planned activities of the interventions will be monitored and recorded. The primary outcome (LOS) data are collected from medical records and do not rely on patient self-reporting. To reduce the risk of selection bias, eligible women will be offered the choice between a face-to-face meeting and a telephone conversation for information about the study, informed consent, and randomization, accommodating women living farther from the hospital.

The ChroPreg trial will provide an extensive evaluation of a coordinated, individualized, and specialized maternity care intervention for pregnant women with chronic diseases. This trial will be among the first of its kind and will help clinicians and policy makers to make evidence-based decisions when developing and implementing efficient, woman-centered, and cost-effective maternity care interventions for women with chronic disease.

To conclude, this paper outlines the background, aim, and methods of an RCT in which the ChroPreg intervention plus standard care is compared with standard care alone in a population of pregnant women with chronic disease. We hypothesize that the sum of active components in the ChroPreg intervention will reduce the overall need for hospitalization and enhance the psychological well-being and satisfaction with care for the participants.

## Trial status

Recruitment of participants was initiated October 1, 2018, and is anticipated to continue until January 31, 2020, and data collection will be concluded by June 1, 2020. By May 22 2019, 130 participants have been included in the Trial. No interim analyses will be performed.

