**Methods/design:**

This two-arm parallel group RCT will be conducted from October 2018 through June 2020 at the Department of Obstetrics, Copenhagen University Hospital, Rigshospitalet, Denmark. Pregnant women with chronic diseases are invited to participate; women will be randomized and allocated 1:1 to the ChroPreg intervention plus standard care or standard care alone. The ChroPreg intervention consists of three main components: (1) coordinated and individualized care, (2) additional ante- and postpartum consultations, and (3) specialized midwives. The primary outcome is length of hospital stay during pregnancy and in the postpartum period, and secondary outcomes are psychological well-being (five-item World Health Organization Well-Being Index, Edinburgh Postnatal Depression Scale, Cambridge Worry Scale), health-related quality of life (12-Item Short Form Health Survey), patient satisfaction (Pregnancy and Childbirth Questionnaire), number of antenatal contacts, and pregnancy and delivery outcomes. Data are collected via patient-administered questionnaires and medical records.

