### Inclusion and exclusion criteria

The Danish Health Authorities define chronic disease as a prolonged disease or a disease that continually recurs [30]. Eligible participants will be pregnant women with one or more chronic diseases diagnosed before pregnancy and for which the pregnant woman is followed by an obstetrician during pregnancy, aged ≥ 18 years, able to understand spoken and written Danish, give informed consent, pregnant with a single live fetus, and be between weeks 12 and 19 of pregnancy at the time of inclusion. Potential participants will be excluded from the study for the following reasons: multiple pregnancy, substance abuse, psychiatric disease as the only chronic disease, and pregnant women with diabetes and heart disease (these women already receive specialized care programs at Rigshospitalet).

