### Sample size calculation

A total of 258 women will be enrolled in the study. The sample size was determined using unpublished data on 426 pregnant women with chronic diseases hospitalized at Rigshospitalet during pregnancy and in the postpartum period in 2017. The average LOS during pregnancy was 3.9 days; however, due to a right-skewed distribution, log-transformed LOS was used as the outcome for the sample size calculation. Therefore, the effect of the intervention is expressed as a ratio. We expect a reduction of 25% in LOS in the intervention group compared with the control group. This corresponds approximately to a mean reduction of 1 day of hospitalization and to an improvement of log (1 – 0.25) = − 0.29 on the logarithmic scale, which we consider a realistic and clinically significant effect size. The standard deviation (SD) of number of days in the hospital on a logarithmic scale was 0.80. With a difference of 0.29 and SD of 0.80, a power of 0.8, and a significance level of 0.05, an analysis by two-sample *t* test requires 123 women in each group. We expect a maximum of 5% to be lost to follow-up, leading to a total of 129 women needed to be enrolled in each group (Fig. 1).

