### Outcome measures

Data will be collected from medical records and electronic self-administered questionnaires and will be obtained at baseline (t1) and three times during the study period: at 33–37 weeks of gestation (t3), at 2 weeks after delivery (t4), and at 2 months after delivery (t5) (Fig. 2). The participants will complete the first electronic questionnaire after signing the informed consent to participate and before randomization. The subsequent questionnaires will be sent as a link in an e-mail.

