#### Primary outcome

The primary outcome is LOS measured as the number of days (mean and SD) spent in the hospital from inclusion in the study and until 2 weeks after delivery. All participants are expected to have a minimum of 1 day of hospital stay in relation to the delivery, because this population is a high-risk population in which home birth is advised against. Should a woman nevertheless have an unplanned home birth, she will expectedly be transferred to the hospital for postpartum.

LOS was chosen as the primary outcome because it is a widely used outcome in health care research [33, 34]. For this trial, a reduction in LOS covers at least two important outcomes in health care research: (1) the patient perspective with a reduced need for hospitalization, which is an expression of better quality of health care received by the patients, and (2) the health economics perspective with reduced health care costs in connection with days of hospitalization.

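### Data collection is set to end 122 days after the last planned inclusion, too early for late recruits to complete the primary outcome window or the 2-month follow-up

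*Protocol article*

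**What the plan says.** All quotes are from the protocol article.

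- **Trial status:** recruitment, open since the start of October 2018, "is anticipated to continue until January 31, 2020, and data collection will be concluded by June 1, 2020". The article reports 130 inclusions as of May 22, 2019.
- **Abstract, Methods/design:** the trial "will be conducted from October 2018 through June 2020".
- **Inclusion and exclusion criteria:** a woman must "be between weeks 12 and 19 of pregnancy at the time of inclusion".
- **Primary outcome:** LOS is the number of days "spent in the hospital from inclusion in the study and until 2 weeks after delivery". Every woman is expected to have at least 1 day of stay around the delivery. The Aim section gives the same window.
- **Outcome measures:** questionnaires follow at 2 weeks (t4) and 2 months (t5) after delivery.
- **Sample size calculation:** 258 women in total, with the allowance "We expect a maximum of 5% to be lost to follow-up".

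Nothing in the article restricts late inclusions, shortens their follow-up or extends data collection for them.

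**The concern.** A woman who enters at week 12 has about 28 weeks to go to a 40-week delivery; one who enters at the end of week 19 has about 20. The primary window adds 2 weeks to that and t5 adds 2 months. The calendar leaves 17.4 weeks after the last planned inclusion, so the stated dates cannot all hold.

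If June 1 were enforced, late recruits would lose all or part of the delivery stay, which is the one stay that every participant is expected to have. The loss would depend on gestation at birth: among late recruits, earlier births would be more often complete. Preterm delivery is itself a secondary outcome, so this would not be a random loss. Dropping these women would weaken the intention-to-treat comparison; keeping them would understate their LOS. The t5 measures, including breastfeeding at 2 months, are more exposed because that point falls later.

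**Working it through.** **1. The plan's own sample size.** Inputs from Sample size calculation: difference log(0.75) = −0.288, SD 0.80, two-sided 5% (two-sidedness assumed), power 0.80. The two-sample t test needs 122.4, so 123 per group, as stated. 123/0.95 = 129.5, against the stated 129. The sample size is not in dispute; the 5% allowance is the yardstick used below.

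**2. Gestation at the end of data collection, last-day inclusion.** January 31 to June 1, 2020 is 122 days = 17 weeks + 3 days. Weeks 12 to 19 are read as 12+0 to 19+6, and 2 months as 61 days.

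| Included January 31 at | Gestation on June 1 | Must deliver by, for LOS (−14 days) | Must deliver by, for t5 (−61 days) |
|---|---|---|---|
| 12+0 | 29+3 | 27+3 | 20+5 |
| 19+6 | 37+2 | 35+2 | 28+4 |

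No term birth (37+0 or later) fits either column. With June 30 instead, the LOS limits become 31+4 and 39+3.

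**3. Latest inclusion date that completes by June 1.** Formula: June 1 − (gestation at birth − gestation at inclusion) − 14 or 61 days.

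| Birth at | LOS, from 12+0 | LOS, from 19+6 | t5, from 12+0 | t5, from 19+6 |
|---|---|---|---|---|
| 37+0 | Nov 25, 2019 | Jan 19, 2020 | Oct 9, 2019 | Dec 3, 2019 |
| 39+0 | Nov 11, 2019 | Jan 5, 2020 | Sep 25, 2019 | Nov 19, 2019 |
| 40+0 | Nov 4, 2019 | Dec 29, 2019 | Sep 18, 2019 | Nov 12, 2019 |

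Some January inclusions near the end of week 19 can therefore complete LOS. One included on January 1 at 19+6 does so if she delivers by 39+4. For t5, the latest date for any term birth is December 3, 2019.

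**4. Share of women affected.** The article gives no distribution of gestation at birth or at inclusion. Assumptions: inclusion uniform over weeks 12 to 20, delivery normal with mean 39 weeks and SD 2, even accrual from October 1, 2018. Two recruitment ends are used: January 31, and the date implied by the reported pace (130 in 233 days = 0.558 per day; 258/0.558 = 462 days, about January 6, 2020). Ranges in brackets use a fixed delivery at 38 to 40 weeks.

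| Recruitment ends | Data collection ends | LOS incomplete | t5 not reached |
|---|---|---|---|
| January 31 | June 1 | 11% (9–12%) | 21% (19–22%) |
| January 6 | June 1 | 6% (5–8%) | 16% (15–18%) |
| January 31 | June 30 | 5% (4–6%) | 15% (13–16%) |
| January 6 | June 30 | 2% (1–2%) | 10% (8–11%) |

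Of 258 women, the first row is about 28 without complete LOS and 53 without t5.

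**5. Power if incomplete LOS is treated as missing.** Take a 10.5% loss, close to the first row, on top of the planned 5%: 258 × 0.95 × 0.895 / 2 ≈ 110 per arm. The standardized difference is 0.288/0.80 = 0.36, and the t test then has power 0.757, about 76% against the planned 80%.

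**The case against.** Four points can be made for the plan.

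- **LOS comes from medical records, as the Discussion says.** It can be retrieved after June 1 without contacting the woman, and the outcome is defined per woman, not by calendar date. Nowhere does the article say that LOS is cut at June 1 or that the database locks then. This stands. A reader might infer that the plan truncates LOS and breaks intention-to-treat; the text supports that only if the planning date overrides the outcome definition. It helps t5 less, because a questionnaire has to be sent at its time.
- **January 31 is only anticipated.** At the reported pace the trial fills about January 6. This roughly halves the LOS shortfall but does not remove it.
- **The abstract allows the whole of June 2020.** This also about halves the LOS shortfall. With both favourable readings together LOS falls to about 2%, inside the 5% allowance, but t5 stays near 10%.
- **Not every late recruit is lost.** A reader might infer that no January 2020 inclusion who delivers at term can complete LOS. The dates do not support that, as step 3 shows. It is true of last-day inclusions, and of any term birth after inclusion from January 20 onward.

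None of these reconciles the stated dates with the follow-up schedule.

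**Conclusion.** The point holds as an inconsistency between the calendar in Trial status and the follow-up that the article itself defines. The conflict rests on date arithmetic alone and does not depend on the assumed delivery distribution.

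Its size does depend on assumptions. Against June 1, incomplete LOS is about 6 to 11% and missing t5 about 16 to 21%, according to when recruitment ends. On a June 30 reading the figures are about 2 to 5% and 10 to 15%. So the 5% allowance is exceeded for LOS under the June 1 date and for t5 under every reading, before any ordinary dropout. It would be too strong to say that the allowance is exceeded for LOS on every reading.

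The consequences for the primary analysis (missing or truncated delivery stays, selection by gestation at birth, power of about 76%) are conditional on June 1 being applied as a hard cut-off. The plan should exclude that possibility.

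**What to change.** Define the end of data collection by the last included woman's follow-up instead of a fixed date. For inclusion up to January 31, 2020 at week 12 with birth by 42 weeks (an assumed upper limit), delivery is by August 28, 2020. The LOS window then closes about September 11, 2020 (+14 days) and t5 falls about October 28, 2020 (+61 days). State that the database is not locked before then, and bring the abstract and Trial status into line.

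The cost is a date amendment and a lock about five months later, with no extra participants or visits. At the article's last count 130 of 258 women were enrolled, so the change could still be made during recruitment.

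Closing recruitment early to keep June 1 is not a sound alternative. Full t5 follow-up would require stopping in about mid-September 2019. At the reported pace that gives about 195 women (349 days × 0.558), about 93 per arm after 5% loss, and power of about 68%.

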## Data Availability

The datasets used and/or analyzed during the current study are available from the corresponding author on reasonable request.

## Abbreviations

CONSORT: Consolidated Standards of Reporting Trials
CWS: Cambridge Worry Scale
EPDS: Edinburgh Postnatal Depression Scale
GP: General practitioner
LOS: Length of hospital stay
PCQ: Pregnancy and Childbirth Questionnaire
RM: Regular midwife
SD: Standard deviation
SM: Specialized midwife
SPIRIT: Standard Protocol Items: Recommendations for Interventional Trials
TIDieR: Template for Intervention Description and Replication
WHO-5: World Health Organization Well-Being Index
